### Ethical and legal aspects

This study protocol was approved by the Ethics Committee of the College of Professional and Continuing Education (RC/ETH/H/0029) and was registered in the Chinese Clinical Trial Registry (ChiCTR2200063370) on 5 September 2022. All participants will be asked to agree and sign an informed consent form to participate in the study.

### Eligibility criteria

The target group of this research is the community-dwelling older people with possible sarcopenia or at risk of falls in Hong Kong. The inclusion criteria and the exclusion criteria are listed in Table 1. The diagnosis of possible sarcopenia is based on the recommendation of the Asian Working Group for Sarcopenia 2019 (AWGS) [27] to assess the SARC-CalF scores, muscle strength and physical performance. The perceived fear of falls is measured by the Chinese version of Fall Efficacy Scale-International (FES-I). The Mini-Mental State Examination (MMSE) determines if participants show signs of cognitive impairment. Medical clearance will be performed according to the guidelines of the American College of Sports Medicine (ACSM).

**Table 1 Tab1:** Inclusion and exclusion criteria

Inclusion criteria	Exclusion criteria
• permanent residents of Hong Kong • aged 65 years or above living independently at home • diagnosed with possible sarcopenia and/or having had either a fall in the past year or fear of falling with a score of ≥ 20 points on FES-I • able to speak and listen to Cantonese • able to walk without mobility aids in their home	• diagnosed with dementia or cognitive impairment, Mini-Mental State (MMSE) < 25 • severe vision impairments that do not permit the use of a tablet, reading of the exercise booklet, and completing the activity diaries • unable to pass the preparticipation Health Screening of the ACSM and the subsequent medical clearance • regular physical activities in the past 6 months based on the definition of WHO [28]

### Sample size calculation

In Hong Kong, there are 1,322,000 residents who are aged 65 years or above [29] and it is estimated that 118,980 of them suffer from sarcopenia (prevalence is 9% for those aged 65 or above [30, 31] and 264,400 of them have had at least one fall in the past year [1]. Calculations were performed using G*Power software and an assumed effect size of 0.367 based on a previous study by Benavent-Caballer et al. [32] on the Time Up and Go Test. Considering a 95% confidence level, a power of 80%, and 20% attrition rate (including mortality) [33], a sample size of at least 92 are required.

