The Otago Exercise Programme (OEP) is an evidence-based fall prevention programme developed in the late 1990s [12, 13]. It consists of five warm-up exercises (head movement, neck movement, back extension, trunk movement and ankle movement) and 17 strength and balance exercises. The original programme was designed as a home-based exercise for older people with guidance and monitoring provided by trained professionals [14]. Many studies have implemented the OEP as an intervention programme for older people to prevent falls and demonstrated positive outcomes, including reduced fall-related injuries and improved functional mobility and balance [15–21]. Similar results were observed in a modified OEP too. The modified formats included additional multisensory balance exercises, augmented reality, training in groups and a DVD delivery format. The OEP in a group is preferable as exercising in a class can offer additional psychological and social benefits [22]. In addition, engagement between the participants and instructors is an essential factor for exercise maintenance, as demonstrated by Davis et al. [23] who delivered the OEP by video along with a single visit by a physical therapist. Compared with studies that involve more participant interaction, the OEP group with less participant interaction resulted in a higher rate of loss to follow-up, with approximately 29.5% of participants failing to complete the post-intervention assessment. Thomas et al. [24] believe that maximizing compliance can improve health outcomes. The OEP is more suitable for older adults who are more prone to falls and less active as the movements required in the exercises are straightforward and of low intensity. However, it lacks interesting variations of movements that may affect compliance [25]. The number of dropouts of OEP modified formats reached 30% [22].

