### Randomization and blinding

After the screening phase, ten community centres will be coded and then randomized such that a similar number of centres will be allocated to either the tele-exercise group (TE) or community-based group (CB) in a concealed, blinded fashion to minimize cross-over contamination between the groups. An independent assistant will oversee the randomization procedures and allocation sequence. Around ten participants will be recruited from each centre. The assessments will be performed by trained outcome assessors who will be blinded to the group assignments. It is impossible to blind the participants in the training mode. However, they cannot communicate with other groups of participants because they are recruited from different locations. The instructors and researchers will not be blinded and will be asked to refrain from discussing the group assignments of the participants with the outcome assessors.

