### Statistical analysis

Descriptive data of the two groups including age, risk of falls, body mass index, muscle mass, and activity level at the baseline will be analyzed by independent t-test to test the homogeneity of the physical characteristics between the two groups. We will use an intention-to-treat analysis based on all randomized participants following the guidelines on randomized controlled trials [43]. We will perform a sensitivity analysis for missing data. The Kolmogorov-Smirnov one-sample test will confirm the normal distribution of all the measurement variables. A two-way repeated measures ANOVA will be performed for all the outcome measures, accounting for the group (TE and CB) and the interaction term between group and time. The p-value will be set at 0.05 for all tests. All statistical analyses will be carried out using SPSS, version 26.0 (IBM Co., Armonk, NY) by an independent statistician who will not be involved in the outcome assessment. Missing data will be complemented by using the multiple imputation method.

Both groups of participants will also be invited to attend focus group interviews with an experienced qualitative researcher. The Theory Domain Framework will be adopted to examine the determinants of behaviour change [44]. Data analysis will follow a framework approach [45] and use Qualitative Data Analysis (QDA) Miner 5 of Provalis Prosuite, which is qualitative data analysis software.

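### The stated 80% power for 92 participants cannot be reproduced for a two-arm, four-time-point design and shows no allowance for randomising ten centres

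*Protocol article*

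**What the plan says.** The section Sample size calculation uses G*Power with "an assumed effect size of 0.367 based on a previous study" of the Timed Up and Go test. It then states: "a power of 80%, and 20% attrition rate (including mortality) [33], a sample size of at least 92 are required". It does not say whether 0.367 is Cohen's d or Cohen's f. It also does not name the test, the number of measurements, a correlation between them, an ICC or a design effect.

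The section Recruitment treats 92 as the total enrolled and as the point at which recruitment stops; Trial Status repeats this.

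The section Randomization and blinding allocates community centres, ten of them, in similar numbers to the two arms. It adds: "Around ten participants will be recruited from each centre". The trial is therefore cluster-randomised, with about five centres per arm.

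The section Statistical analysis plans a two-way repeated measures ANOVA on group and group by time, and fixes the level: "The p-value will be set at 0.05 for all tests". The primary outcomes are measured at baseline and at months 3, 6 and 12, which makes four time points.

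**The concern.** Two things do not fit together. First, a reader who takes the listed inputs and the trial's own layout does not arrive at 92. Second, the listed inputs describe independent participants, whereas the randomisation section describes ten clusters. People from the same centre share a neighbourhood, a recruitment route and a class, so their outcomes may be correlated. Any positive ICC then lowers power below what the same calculation gives for individual randomisation. With only ten centres, the between-centre comparison also rests on 8 degrees of freedom.

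The trial hypothesises that tele-exercise is as effective as the face-to-face programme. A non-significant difference will be read against the claimed 80%. If that figure is not what 92 people in ten centres deliver, a null result will look more informative than it is.

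**Working it through.** **Inputs from the protocol article.** Effect size 0.367; 95% confidence (two-sided 0.05 taken as the default); power 80%; attrition 20%; 92 enrolled; two arms; four time points; ten centres. Completers: 92 × 0.8 = 73.6, about 74, or 7.36 per centre. Enrolled per centre: 92/10 = 9.2.

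**Assumptions, not in the document.** ICC 0.01 to 0.10. Baseline-to-follow-up correlation 0.5 to 0.7 where adjustment is considered. Correlation 0.5 between repeated measurements where an option needs one.

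**Step 1: try to reproduce 92** (80% power, exact noncentral t or F; enrolled = completers/0.8).

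| Reading, two arms | Completers | Enrolled |
|---|---|---|
| 0.367 as d, t-test | 236 | 295 |
| 0.367 as f (d = 2f = 0.734), t-test | 62 | 78 |
| f, four time points, between-group effect | 40 | 50 |
| f, four time points, interaction, G*Power default | 12 | 15 |
| f, four time points, interaction, Cohen option | 84 | 105 |
| f, four time points, MANOVA | 86 | 108 |

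None gives 92. With 74 completers and no clustering, power is about 34% under d and 88% under f.

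**Step 2: design effect.** DE = 1 + (m − 1) × ICC, with m = 9.2. The last column takes a design with exactly 80% power under individual randomisation and computes Φ((1.96 + 0.842)/√DE − 1.96). This normal approximation does not yet include the loss from having 8 degrees of freedom.

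| ICC | DE | 92 × DE, rounded up | 80% becomes |
|---|---|---|---|
| 0.01 | 1.08 | 100 | 77% |
| 0.02 | 1.16 | 108 | 74% |
| 0.05 | 1.41 | 130 | 66% |
| 0.10 | 1.82 | 168 | 55% |

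**Step 3: power of 92 in ten centres.** In SD units, the variance of the difference between arms (five centres each, 7.36 completers per centre) is V = 4 × (ICC + (1 − ICC)/7.36)/10. Noncentrality is d/√V, referred to t on 8 df. For baseline adjustment with correlation r, V is multiplied by 1 − r², which assumes the same reduction between and within centres.

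Example at ICC 0.05: V = 4 × (0.05 + 0.95/7.36)/10 = 0.0716 and √V = 0.268. The noncentrality is 0.367/0.268 = 1.37 under d and 0.734/0.268 = 2.74 under f.

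| ICC | d, unadjusted | f, unadjusted | f, r = 0.5 | f, r = 0.7 |
|---|---|---|---|---|
| 0 | 28% | 79% | 89% | 97% |
| 0.02 | 26% | 74% | 85% | 95% |
| 0.05 | 23% | 67% | 79% | 92% |
| 0.10 | 19% | 58% | 70% | 85% |

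Under d, adjustment at r = 0.7 gives 45%, 39% and 33% at ICC 0.02, 0.05 and 0.10.

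**The case against.** The strongest reply is that the inputs are incomplete, so failure to reproduce 92 does not show that it is wrong, and a journal article may condense software settings. This stands in part. Two groups with three time points come close: the Cohen option needs 74, and 74/0.8 = 92.5; MANOVA needs 76, and 76 × 1.2 = 91.2. A baseline-adjusted comparison with 0.367 as d can also be tuned to 92 by choosing a correlation near 0.83: 236 × (1 − 0.83²) = 73.4, and 73.4/0.8 = 91.8. But the protocol lists four time points and gives no correlation. All of these settings also assume independent participants, so they leave the clustering problem where it was.

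A reader might infer that the trial lacks its stated power. The documents do not support that as a flat statement. If 0.367 is f, the result turns on unstated quantities. The adjusted figures above lie on both sides of 80%. A four-time-point between-group test on 8 df (correlation 0.5) gives 92%, 86% and 78% at ICC 0.01, 0.05 and 0.10. At correlation 0.9 it gives about 80%, 71% and 61%.

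A reader might also infer that 20% attrition is too low, because the Background says: "The number of dropouts of OEP modified formats reached 30" per cent. That does not contradict the plan. The 20% has its own cited source, the 30% is an upper value across modified formats, and the 29.5% also mentioned there comes from a video format with little interaction. This trial plans supervised classes with regular calls.

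**Conclusion.** The point holds in a limited form. For two arms and four time points, none of the standard readings gives 92, and the metric and test needed to settle the matter are not stated. The 80% is therefore unsupported. It is overstated to the extent that 92 was sized for individual randomisation, and nothing in the sample size section suggests otherwise.

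The size depends on the reading. Under d, power with ten centres is well below 80% across the ICC and correlation ranges tried. Under f, it lies between 58% and 95% for ICC 0.02 to 0.10, according to whether and how strongly baseline is adjusted for. The ICC and correlation ranges are assumptions, and the 8 df follow from a comparison of ten centres. This is more than missing detail: the protocol itself asserts a power figure while fixing a randomisation scheme that its listed inputs do not cover.

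**What to change.** Keep 92 if that is what is feasible, and restate the calculation for the design actually used:

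- Say whether 0.367 is d or f, and name the test, the time point of the Timed Up and Go comparison and the correlation assumed.
- Add ten centres of about nine, an assumed ICC range (for example 0.01 to 0.10) and 8 between-centre degrees of freedom.
- Replace 80% with the power that 92 in ten centres delivers over that range, or with the expected 95% confidence-interval half-width. With the variance formula above, the half-width is 2.306 × √V. Unadjusted, that is about 0.57, 0.62 and 0.69 SD at ICC 0.02, 0.05 and 0.10. With r = 0.7 it is about 0.41, 0.44 and 0.49 SD.

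The cost is revised text, probably with a less favourable figure. No extra participants or centres are needed, and recruitment can continue unchanged.

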### Recruitment

The potential participants will be recruited from ten community centres in Hong Kong. They will receive information about this study through a series of health talks and posters displayed in their community centres. Interested participants will register in the community centres. Our project assistant will contact them to assess their eligibility according to the inclusion and exclusion criteria and explain the details of the study to them. Eligible participants will sign the informed consent form voluntarily. Recruitment started in September 2022 and will end when 92 participants have been enrolled.

### Randomization and blinding

After the screening phase, ten community centres will be coded and then randomized such that a similar number of centres will be allocated to either the tele-exercise group (TE) or community-based group (CB) in a concealed, blinded fashion to minimize cross-over contamination between the groups. An independent assistant will oversee the randomization procedures and allocation sequence. Around ten participants will be recruited from each centre. The assessments will be performed by trained outcome assessors who will be blinded to the group assignments. It is impossible to blind the participants in the training mode. However, they cannot communicate with other groups of participants because they are recruited from different locations. The instructors and researchers will not be blinded and will be asked to refrain from discussing the group assignments of the participants with the outcome assessors.

### Baseline assessment

The details of the study will be explained to all participants, who will sign the consent form. Assessment will be performed before the intervention period, at the end of the 3rd, 6th and 12th months. The baseline assessments include the Chinese version of Fall Efficacy Scale-International (FES-I), fall incidence, SARC- CalF scoring, right-hand and left-hand grip strength, Timed Up and Go test, Berg Balance Scale, 6-metre walk test, Functional Reach Test, Physical Activity Scale for the Elderly (PASE) [34], Daily activity level, Rosenberg Self-esteem Scale and EQ-5D-3 L. The weight, body fat and skeletal muscle mass will be measured by a bioimpedance scale.

### Interventions

All participants will attend the exercise training 3 days per week for 3 months, under the delivery mode of either tele-exercise or a community-based approach. The community-based group will serve as a positive control as the effectiveness of the OEP to prevent falls is well established [24] and the aims of the current study focus on the effectiveness of the new mode of delivery, i.e. tele-exercise. The exercise programme will be structured with a warm-up, Otago strengthening and balance retraining exercises, “workouts on-demand” and cool down (Table 2). The OEP consists of five warm-up exercises (head movement, neck movement, back extension, trunk movement and ankle movement) and 17 strength and balance exercises [14]. For the “workouts on-demand” part, participants will express their needs such as focusing more on the upper body, flexibility, or strength. The instructor will present real-time demonstrations to promote exercise empowerment. Both groups of participants will be divided into classes of 9–10 people. In addition, they will be asked to maintain their daily number of steps at 10,000 or increase their step count by 3,500 compared with their usual habit. They will be required to record all the exercises they perform, the number of steps achieved and the fall incidence during the 12 months.

**Table 2 Tab2:** Lesson plan for both TE and CB groups

Content	Duration
Warm-up (dynamic and static stretching)	~ 10 min
A short pause to allow participants to be ready for the next part and interact with the instructor	
Otago exercise programme-strengthening exercises	~ 10 min
A short pause to allow participants to be ready for the next part and interact with the instructor	
Otago exercise programme- balance retraining exercises	~ 10 min
Workouts on-demand allow participants to - express their opinions on the exercises - request targeted training for specific body parts at a higher or lower level	5–10 min
Cool down	~ 10 min

#### Intervention-tele-exercise group

For the TE group, the exercise programme will be delivered via Zoom (Zoom Video Communications Inc.), which allows online communication with participants, screen sharing, and video recording. To run the exercise training smoothly, participants will be given a tablet computer with a stand if they do not have suitable devices. Those who do not have a Wi-Fi connection will be provided with data sim cards that allow internet access. Home visits will be arranged before the intervention to support the participants technically in using and setting up online communication applications in their homes. The position of the tablet, the chair and the participant for the best visual effect and interaction will be marked and recorded. A sturdy chair will act as a nearby support for the participant during training. The participants will be reminded to turn on their tablet and the Wi-Fi connection before the class so that the project team will control the tablet remotely and solve most technical problems immediately. Participants will attend the first lesson in the community centre to familiarise themselves with the exercise safety rules and the OEP. After that, all the training sessions will be delivered online. To enhance the interaction, the participants will be required to turn on their camera and microphone. The team will monitor the progress of the participants regularly.

#### Safety measures for the tele-exercise group

The team will conduct a home visit to every participant of the TE group to ensure exercise safety and offer technical support. The setup of the tablet, as well as the home environment of the participants will be checked at the beginning of every lesson. The participants will be asked to perform all the exercises of the OEP under the supervision of the instructor during the first lesson in the community centre. All participants will start the exercises at the beginner level (level A) for which they will be asked to hold the support for all the standing and walking exercises. Among the Otago exercises, backward walking may require more attention. The team will also estimate the space required for walking and the upper body exercise for the “Workouts on-demand” session. If 4 sets of 10 steps cannot be performed due to limited space, the participant will be asked to do 10 sets of 4 steps instead.

 In addition, the participants will be reminded to wear appropriate exercise gear including non-slip sport shoes as well as stay hydrated. If the participants cannot follow the Zoom training properly, another home visit will be conducted. If an incident such as a fall occurs, we will endeavour to communicate with the participant to ascertain if he or she is responsive and understand the seriousness of the incident. If the participant falls unconscious, we will call for emergency help and contact his or her relatives immediately. A safety protocol has been developed to guide the emergency procedures (Fig. 3).

**Fig. 3 Fig3:**
[figure not shown]
Sample safety protocol

#### Intervention-community-based group

The team will organize classes in the community centres. The location of the course will be based on the residence of the participants being recruited. The instructor will deliver the OEP to the participants face to face. Like the TE group, the instructor will regularly monitor and review their progress.

#### Intrinsic differences between tele-exercise and community-based group

There are intrinsic differences in the delivery mode between CB and TE. In CB, participants have direct communication with the instructor and their classmates. The instructor can correct the movements of participants verbally and physically. In contrast, in TE, the instructor can observe all the participants in real time as their images are projected onto a large screen (Diagonal: 100 inch). The instructor can only correct the movement of the participants verbally but not physically (Table 3). On the other hand, we will pin the image of the instructor to the screen of all the participants. Participants can only observe the movements of the instructors on their screens and not those of their peers.

**Table 3 Tab3:** Intrinsic differences between TE and CB

	TE	CB
Mode of delivery	Online via Zoom	Face-to-face
Location of the class	Participants’ home	Community centre
Interaction		
(i) verbally between the instructor and participants	Directly with minimal delay	Directly
(ii) verbally between the participants	Possible after class	Possible during and after class

#### Maintenance phase

After 3 months of training, a workshop will be arranged to remind the participants to maintain the exercise habit and achieve a daily step count of > 10,000 steps or increase their step count by 3,500 every three months until they reach 10,000 steps per day. The exercise booklets of our exercise programme will be distributed to all participants. The exercise videos will be sent to them via WhatsApp, or presented to them in a way that they can be easily accessed. They will be reminded by phone at least twice per month to record their exercise and step count in the diary provided.

